### Study design and setting

A multiple baseline study [50] will be conducted involving all 56 community health facilities in a single health service in New South Wales, Australia. The service provides comprehensive healthcare to approximately 840000 people residing in metropolitan, regional, rural and remote location, and employs over 1400 community health clinicians who see in total approximately 57000 clients per year.

The study will involve the sequential implementation of a 12 month practice change intervention in three administratively defined groups of community health facilities (Figure 1). The intervention will be implemented in a non-random sequence across the three facility groups.

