### Sample size

Assuming a baseline prevalence of 50% for all forms of preventive care delivery (worst case scenario), the study will have 80% power to detect a difference of between 4.7% to 21.8% in the assessment of each health risk between baseline and follow-up for the three groups at the 1% significance level. Power estimates for the provision of brief advice and referral for all four risk behaviours are conservatively based on the expected number of smokers; as smoking is the least prevalent risk behaviour [1]. The sample in the third group of facilities (which has the shortest follow-up period) is expected to include approximately 450 (20%) smokers in the baseline period and 75 smokers during the follow-up period. With a brief advice prevalence of 50% at baseline, the study will have over 80% power to detect a 20.9% improvement in the prevalence of such care (i.e. a change from 50.0% to 70.9%). Similarly, with an estimated prevalence of 50% for offering a referral prior to the intervention, the study will have over 80% power to detect a 20.9% improvement in prevalence of such care (i.e. a change from 50.0% to 70.9%).

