#### Preventive care delivery

##### Client data

For each outcome, evaluation of intervention effectiveness will involve fitting a segmented logistic regression model, including separate intercepts and slopes at baseline, during the intervention and at follow-up (the three "segments") [74,75]. A statistically significant coefficient for the intercept and/or slope during the intervention or follow-up will indicate a change in the outcome measure following the intervention for each group. Standard errors of coefficients, and hence p-values and confidence intervals, will be estimated using bootstrapping [76]. In the first set of models the outcome of interest will assess client reported assessment of risk behaviour. The second set of models will be restricted to those subjects who report a risk behaviour, with separate models assessing whether or not the community health clinician provided brief advice, or offered a referral.

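### The advice and referral power figures make no allowance for facility clustering, and the bootstrap for the client outcomes does not name its resampling unit

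*Protocol article*

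**What the plan says.** The study is a multiple baseline design "involving all 56 community health facilities in a single health service". Three administrative groups of facilities start the intervention in sequence, and each group serves as its own control (Study design and setting). Clients are sampled at random within each group, with one interview per client (Clients).

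Much of the intervention works at facility level. Support officers are allocated to individual facilities (Educational outreach visits and academic detailing), monthly performance reports go down to service and facility level (Audit and feedback), and media releases are timed to the start in each facility (Community promotion).

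Client data specifies, for each outcome, a segmented logistic regression with an intercept and slope in each of three segments. It names no facility term. On uncertainty it says: "Standard errors of coefficients, and hence p-values and confidence intervals, will be estimated using bootstrapping". No resampling unit is given.

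Sample size bases advice and referral power on group 3 smokers, "approximately 450 (20%) smokers in the baseline period and 75 smokers during the follow-up period". Taking half of these clients as already receiving the care before the intervention, it states that "the study will have over 80% power to detect a 20.9% improvement in the prevalence of such care". The level, "at the 1% significance level", is given in this section only. The section mentions no facility, intraclass correlation or design effect.

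**The concern.** Facilities receive their own support and feedback, so uptake may rise or fade at different rates in different facilities. Clients of one facility then share changes over time. A within-group before-after comparison removes facility differences that stay constant, but not those that change.

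Two things follow. First, power computed from independent clients is too favourable by whatever such change adds to the variance. Second, because the model has no stated facility term, the bootstrap is the only place where clustering could enter the inference. Resampling clients would reproduce the independent-client standard error; resampling facilities would not. The sentence allows either, and it governs all 12 client outcomes (three elements of care for four risks).

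**Working it through.** **1. The stated power.** Inputs from Sample size: n1 = 450, n2 = 75, p1 = 0.500, p2 = 0.709, level 1%. Sidedness is not stated; two-sided matches (z = 2.576).

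- Pooled p = (450×0.5 + 75×0.709)/525 = 0.5299.
- Standard error under the null = √[0.5299×0.4701×(1/450 + 1/75)] = 0.06225.
- Standard error under the alternative = √[0.25/450 + 0.709×0.291/75] = 0.05750.
- Power = Φ[(0.209 − 2.576×0.06225)/0.05750] = Φ(0.846) = 80.1%.

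The detectable difference at 80% power solves to 20.9 points. Variants do not match: one-sided 1% gives 19.4, two-sided 5% gives 17.2, and a continuity correction gives 21.6. The figure is therefore the independent-client result with a design effect of 1. A design effect of 1.1 lowers power to 75%, and 1.2 lowers it to 70%.

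**2. Design effect for the within-group difference.** The protocol gives no ICC, no between-period correlation and no split of facilities. Assumptions: k = 56/3 = 18.7 equal facilities per group; ICC 0.02 to 0.10; CAC = share of facility variance that is stable across periods.

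X = [2·ICC·(1 − CAC)/k] / (1/n1 + 1/n2)

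- Formula A holds total variance at the binomial value: DE = 1 − ICC + X.
- Formula B adds facility variance to it: DE = 1 + X.

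For 450 v 75, X = (0.10714/0.015556)·ICC·(1 − CAC) = 6.89·ICC·(1 − CAC). Power is recomputed with both sample sizes divided by DE.

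| ICC | Stable share | DE (A) | Power (A) | DE (B) | Power (B) |
|---|---|---|---|---|---|
| 0.02 | 80% | 1.01 | 79.7% | 1.03 | 78.7% |
| 0.05 | 80% | 1.02 | 79.2% | 1.07 | 76.6% |
| 0.10 | 80% | 1.04 | 78.2% | 1.14 | 73.2% |
| 0.02 | 50% | 1.05 | 77.7% | 1.07 | 76.6% |
| 0.05 | 50% | 1.12 | 74.0% | 1.17 | 71.5% |
| 0.10 | 50% | 1.24 | 68.1% | 1.34 | 63.5% |
| 0.02 to 0.10 | 100% | 0.98 to 0.90 | 81% to 85% | 1.00 | 80.1% |

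Under A with half stable, the detectable difference is 21.4, 22.1 and 23.2 points for ICC 0.02, 0.05 and 0.10. In the extreme case of no stability at all, A gives power of 65.8% at ICC 0.05 and 53.8% at 0.10.

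**3. Size of a crude before-after test that ignores clustering.** All clients (numbers from Clients): 750 v 1875, 1500 v 1125 and 2250 v 375. The multiplier 0.10714/(1/n1 + 1/n2) is 57.4, 68.9 and 34.4. Actual size at nominal 1% is 2Φ(−2.576/√DE). Under A, for groups 1 / 2 / 3:

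| ICC | 80% stable | 50% stable |
|---|---|---|
| 0.02 | 1.9% / 2.2% / 1.5% | 3.9% / 4.6% / 2.5% |
| 0.05 | 3.7% / 4.4% / 2.4% | 9.5% / 11.5% / 5.6% |
| 0.10 | 7.2% / 8.8% / 4.1% | 18% / 22% / 11% |

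Formula B is slightly higher, at most 9.5% (80% stable) and 22% (50% stable). With fully stable effects, size is just under 1% under A and 1% under B.

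**4. The planned coefficients.** The crude test is not the planned analysis. A simulation of the segmented logistic model (groups 1 and 3, 19 equal facilities, ICC 0.02 and 0.05, stable share 50% to 100%, 600 runs per setting, facility effects that shift between periods) gave independent-client rejection rates of 0.3% to 1.7% at nominal 1% for the follow-up intercept. The crude contrast gave about 3% to 8% at 50% stable. A second simulation, with slowly drifting facility effects and a linear-probability version of the model (ICC 0.05, one-year correlation about 0.6), gave about 1.2% to 4.3% per coefficient contrast in groups 1 and 2, and 1.2% to 1.7% in group 3. At ICC 0.10 the range was about 0.7% to 7%.

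**5. Limit of the reproduction.** Sample size also claims "80% power to detect a difference of between 4.7% to 21.8% in the assessment of each health risk". With independent clients, 50% baseline and two-sided 1%, the within-group detectable differences lie between 6.7 and 9.5 points (3.9 with groups pooled). That range was not reproduced, so the independence finding rests on the 20.9-point figure.

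**The case against.** The strongest objection is that the protocol never says clients are resampled. A facility bootstrap fits the sentence equally well, and choosing a bootstrap over model-based errors is compatible with an intent to handle dependence. A condensed article may leave the unit to an analysis plan that is not shown. This stands against the reading a reader might infer, that the planned standard errors are too small for every outcome. The power basis makes client-level resampling the natural reading, but the text does not state it.

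Three other tempting readings also go too far.

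- **The 1% level will not be held.** The 1% level is given for the power calculation only; Client data sets no level. The sizes in step 3 are for a crude contrast, and inflation for the segmented coefficients is smaller and depends on how facility effects drift.
- **A conventional design effect of 1.5 or 2.0 applies.** That would give power of 57% or 41%. But group 3 smokers number only about 24 per facility at baseline and 4 at follow-up. With 80% of facility variance stable, formula B needs an ICC of about 0.36 or 0.73 to reach those values.
- **The 56 facilities switch separately.** Three groups switch. Stable facility differences cancel within a group, and with fully stable effects nothing is lost.

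None of this restores the stated power. The 20.9-point figure has no allowance for clustering and almost no margin.

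**Conclusion.** The point holds in two parts of different strength.

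The power part is firm: the advice and referral figures treat clients as independent. Under the assumed inputs (18.7 equal facilities per group, ICC 0.02 to 0.10), power for the 20.9-point change is about 73% to 80% across both formulas with 80% of facility variance stable. With 50% stable it is 68% to 78% under formula A and 64% to 77% under B. With full stability it is no lower than stated. The likely loss is modest.

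The inference part is conditional. If clients were resampled, standard errors would be too small to the extent that facility effects vary over time. A crude test at nominal 1% would then have a size of about 2% to 10% (80% stable) or 2.5% to 22% (50% stable), and about 1% or just under if effects are stable. The planned coefficients are affected less. The ICC and between-period correlation are assumptions throughout, since the protocol gives neither.

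**What to change.** In Client data, state that the bootstrap draws whole facilities within each group, keeping all their clients from all periods together. Alternatively, add facility and facility-by-period random effects to the segmented model. In Sample size, restate power and detectable difference over a stated range of ICC and between-period correlation, with the assumed number of facilities per group. Facility-level reporting implies that facility identity is held, but Community health service characteristics lists only team, group and service type, so facility should be added there.

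Two limits should be stated alongside. Facility resampling does not capture time shocks shared by a whole group. And with about 19 facilities per group, calibration needs care: facility-robust standard errors with a normal critical value rejected in 1.2% to 2.8% of runs at nominal 1% in the first simulation in step 4.

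The cost is wording and analysis code, with no new interviews. The downside is wider intervals and a slightly less favourable stated power. Fixing the unit before outcomes are analysed also avoids a later choice between standard errors.

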##### Clinician data

Baseline and follow-up clinician data will be analysed using logistic regression analyses to detect patterns of clinician provision of preventive care at baseline and following the intervention.

##### Acceptability

Client and clinician reported acceptability data will be reported using simple descriptive statistics.

## Discussion

This study aims to assess the effectiveness of a multi-strategic intervention in increasing community health clinician provision of preventive care for each of the four most common chronic disease risk behaviours. The study will enhance the currently limited experimental evidence regarding the effectiveness and acceptability of a multi-strategic practice change intervention in encouraging primary health care providers to address multiple chronic disease risks simultaneously, and in enhancing the provision of preventative care across a large network of community health facilities.
